**LIST OF ABBREVIATIONS AND RELEVANT DEFINITIONS**

| **ABR** | **ABR form, General Assessment and Registration form, is the application form that is required for submission to the accredited Ethics Committee (In Dutch, ABR = Algemene Beoordeling en Registratie)** |
| --- | --- |
| **AUC** | **Area under the Curve** |
| **BMI** | **Body Mass Index** |
| **CA** | **Competent Authority** |
| **CCMO** | **Central Committee on Research Involving Human Subjects; in Dutch: Centrale Commissie Mensgebonden Onderzoek** |
| **CV** | **Curriculum Vitae** |
| **EU** | **European Union** |
| **GCP** | **Good Clinical Practice** |
| **IC** | **Informed Consent** |
| **METC** | **Medical research ethics committee (MREC); in Dutch: medisch ethische toetsing commissie (METC)** |
| **PK** | **Pharmacokinetics** |
| **SPC** | **Summary of Product Characteristics (in Dutch: officiële productinfomatie IB1-tekst)** |
| **Sponsor** | **The sponsor is the party that commissions the organisation or performance of the research, for example a pharmaceutical**  **company, academic hospital, scientific organisation or investigator. A party that provides funding for a study but does not commission it is not regarded as the sponsor, but referred to as a subsidising party.** |
| **Wbp** | **Personal Data Protection Act (in Dutch: Wet Bescherming Persoonsgevens)** |
| **WMO** | **Medical Research Involving Human Subjects Act (in Dutch: Wet Medisch-wetenschappelijk Onderzoek met Mensen** |

**SUMMARY**

**Rationale:** Fentanyl is a strong opioïd and is highly lipophilic. Fentanyl pharmacokinetics are characterised by large inter- and inpatient differences, which may have serious consequences for the activity and toxicity profile of this drug. In this study we explore the influence of BMI and smoking behaviour on the pharmacokinetics (i.e. clearance (CL)) of fentanyl.

**Objective:** Primary objective: To study the relation between BMI and the pharmacokinetics of fentanyl, in patients using a stable dose of the fentanyl patch (Durogesic ®). Secundary objective: to study the relation between smoking and the pharmacokinetics of fentanyl, in patients using a stable dose of the fentanyl patch (Durogesic ®).

**Study design:** explorative cohort study

**Study population:** All patients using a stable dose of a fentanyl (Durogesic ®) patch (for at least 8 days).

**Intervention (if applicable)**: not applicable

**Main study parameters/endpoints:** Pharmacokinetics (Clearance, AUC, etc.)

**Nature and extent of the burden and risks associated with participation, benefit and group relatedness:** This study has an **extremely low** risk for the participating patients. After taking 1 blood sample, the study is finished. There is no direct benefit for the patient.

# INTRODUCTION AND RATIONALE

Pain is a common problem in cancer patients, occurring both in curative settings as well as in palliative settings. Opioids are often used to treat cancer pain. Fentanyl is one of the most widely used opioids.

Several preparations of fentanyl are currently available . The transdermal fentanyl patch is developed for maintenance medication in chronic pain and is the most commonly used form. Patches are available in different sizes, consistent with specific delivery doses of these patches (12ug/hr, 25ug/hr, 50ug/hr, 75ug/hr or 100ug/hr). Fentanyl is absorbed through the intact skin and a constant dose of drug is absorbed. Two different patches have been developed; a reservoir patch and a matrix patch. These patches differ in the way fentanyl is stored. However farmacokinetically, they are comparable . Nowadays, only the matrix patch is used in clinical practice.

After placement of the patch, the plasma fentanyl concentration gradually increases. After 72hrs the patch has to be changed for a new one, as a stable diffusion of the drug through the skin is no longer guaranteed. Steady state concentrations are approached when a second transdermal fentanyl patch is sticked on the skin . Removing the patch will not immediately lead to diminished fentanyl concentrations because of the amount of fentanyl stored in subcutaneous depots, and therefore systemic concentrations will gradually decrease.

Fentanyl is a drug that is highly lipophilic and binds strongly to plasma proteins. Fentanyl is more potent than morphine at equipotent dose levels . The metabolism of fentanyl takes place primarily in the liver . Fentanyl is mainly oxidized into the inactive metabolite norfentanyl by the CYP3A4 iso-enzyme . Less than 1% is metabolized to despropionyl-fentanyl, hydroxyfentanyl, and hydroxynorfentanyl, which are also inactive metabolites. Fentanyl is mainly excreted renally and for a minor part through the feces. The large majority of the fentanyl is excreted as the metabolites mentioned; 10% as unchanged drug .

Unfortunately there is a wide pharmacokinetic intra- and interpatient variability in patients using a fentanyl patch. It is largely unclear which factors contribute to this variability . It is crucial to know which factors influence fentanyl concentrations because of the risk of over- and underdosing of fentanyl. An overdose of fentanyl could lead to serious complications, including respiratory depression or ultimately death, while underdosing fentanyl may lead to inadequate pain relief.

Fentanyl is dosed by titration. When pain is inadequately treated and side effects are manageable the fentanyl dose is usually increased. Dose finding by titration cannot be used in patients who switch from another opioid to fentanyl. Usually these patients start with more or less the equi-analgetic dose of fentanyl. Especially in these cases it would be extremely helpful if could be predicted if these patients are at risk for under- or overdosing of fentanyl.

Fentanyl is highly liphophilic and will be absorbed by the subcutaneous fat-tissue. We hypothesize that higher fentanyl concentrations will be reached when the patch is used by patients with thicker subcutaneous fat layers, represented by patients with a higher body mass index (BMI). Most farmacokinetic studies with fentanyl are performed in healthy volunteers or in patients undergoing elective surgery. Unfortunately, not all studies reported the BMI of the included patients. In studies with healthy volunteers BMI was under 30kg/m2 or mean weight between 70 and 80 kg . Most studies in patients undergoing surgery only included patients with a weight under 100kg . Just a few studies have studied fentanyl farmacokinetics in cancer patients. One of these studies showed significantly lower fentanyl concentrations in cachectic patients (mean BMI 16 kg/m2) than in normal weigth patients (mean BMI 23 kg/m2) using a fentanyl patch for 48 - 72hr . Two other farmacokinetic studies in cancer patients did not show significant differences between normal weight patients compared to cachectic patients . However, in these studies patients in the lowest BMI group had a BMI ≤ 18.5 instead of a BMI of 16 in the study of Heiskanen .

Another factor that can be of influence on the pharmacokinetics of medication is cigarette smoking. As 25% of the population in the Netherlands smokes cigarettes, male vs female is 27% -23 %, probably a significant part of the fentanyl users also are smokers .. .

The polycyclic aromatic hydrocarbons in cigarette smoke are believed to be responsible

for the induction of cytochrome P450.. A study with erlotinib showed a significantly decreased AUC in smokers compared to nonsmokers . Both erlotinib and fentanyl are mostly metabolized by CYP 3A4. A small part of the metabolism of erlotinib is also influenced by CYP 1A1. Cigarette smoke induces CYP 1A1 and can lead to a cascade, which also involves CYP 3A4, thereby influencing the clearance of erlotinib . Probably, it also influences the metabolism of fentanyl. A study from our group with irinotecan showed a lower exposure to SN-38 (the active irinotecan metabolite) in smokers compared to non-smokers. The hypothesis was that irinotecan is highly sensitive to CYP3A induction and that this is modulated by cigarette smoking .. Possible influence of smoking on clearance of fentanyl is important to know. Terminally ill patients often change their habits in the last part of life. Heavy smokers are physically not able to smoke as much as they did before, or occasional smokers smoke more because of stress. Both scenarios can potentially influence the fentanyl clearance. This may result in over- or underdosing of fentanyl, causing intoxication or ineffective pain treatment.

As a result of these earlier publications, in this study we want to determine which patient characteristics influence the pharmacokinetics of fentanyl.

# OBJECTIVES

Primary Objective:

- to study the effect of BMI on pharmacokinetics of fentanyl by comparing the AUC between patients with a BMI < 20 and patients with a a BMI > 25, both using a stable dose of the fentanyl patch (Durogesic ®).

Secundary Objective:

- to study the effect of smoking on pharmacokinetics of fentanyl by comparing the AUC between smokers and non-smokers, both using a stable dose of the fentanyl patch (Durogesic ®).

Stable dose is defined as using the same dose of fentanyl during at least 8 days.

# STUDY DESIGN

This is a single-center pharmacokinetic cohort study. The trial will be performed at the Erasmus MC Cancer Institute, department of Medical Oncology.

Patients with a stable dosage of fentanyl used through a patch can be included. Stable dose is defined as at least 8 days using a stable fentanyl dosage. Blood samples are always taken on the 2nd day of the used patch.

Patients will be asked to stick a fentanyl patch (Durogesic ®) during 3 periods at the upper arm. During the third period, a venous blood sample will be taken. This blood sample will be taken at the same moment as a regular blood sampling is performed.

After taking the blood sample the patient has finished the study.

# STUDY POPULATION

## Population

Patients for the study will be recruited at the outpatient department of Medical Oncology in both locations of the Erasmus MC Cancer Institute.

## Inclusion criteria

In order to be eligible to participate in this study, a subject must meet all of the following criteria:

- age  18 years;
- stable use and dose of fentanyl patch (Durogesic ®) for at least 8 days, irrespective of the dose used;
- written informed consent.

## Exclusion criteria

A potential subject who meets any of the following criteria will be excluded from participation in this study:

- Using fentanyl as rescue medication (other opioids are allowed)
- Serious psychiatric illness, confusion of intellectual disability
- The use of strong cytochrome P450 inhibitors or inducers.

## Sample size calculation

BMI

With a suggested inter-patient variability in fentanyl pharmacokinetics of 25%, a power of 0.8 and two-side testing (P <0.025) at least **20 evaluable patients** in each group are required to determine a difference in exposure between the two BMI-groups of 25%. To evaluate the differences in plasma fentanyl concentrations the Student’s t test is used. Smokers and non-smokers will be distributed equally in these BMI-groups.

Smoking

Around 25% of the Dutch population smokes. In this study at least 20 patients have to be smokers and at least 20 have to be non-smokers to detect a similar difference in exposure of 25%. Patients can be included independently of their BMI. Smokers are patients who are smoking daily any kind of tobacco or e-cigarettes. Non-smokers are patients who quit smoking at least one month before PK sampling.

In conclusion, the cohort exists of:

- At least 20 patients with BMI < 20 (about 5 smokers)
- At least 20 patients with BMI > 25 (about 5 smokers)
- At least 20 patients defined as smokers
- At least 20 patients defined as non-smokers
- Dependent on the number of smokers in the extreme BMI groups: about 40 patients with

20 ≤ BMI ≤ 25 (about 10 smokers)

In total we will include a maximum of 80 patients.

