# STATISTICAL ANALYSIS

The clearance of all different samples is calculated. This is independent of the dose because of linear pharmacokinetics. After this calculation we will use the Student’s t test to compare the clearance for fentanyl in patients with a BMI < 20 compared to a BMI > 25 and for smokers versus non-smokers.

For all 4 of these groups at least 20 patients have to be included.

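### The two tests are sized at a fixed two-sided 0.025 each; Holm's procedure would keep the same inferred 5% family-wise error and never reject less (an optional efficiency gain)

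*Protocol*

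**What the plan says.** Section 4.4 (Sample size calculation) takes "a suggested inter-patient variability in fentanyl pharmacokinetics of 25" per cent and "a power of 0.8 and two-side testing (P <0.025". Its result, given as a minimum, is that "20 evaluable patients in each group are required". The effect behind this number is described as being able "to determine a difference in exposure between the two BMI-groups of 25" per cent. The smoking paragraph sets a minimum of 20 smokers and adds that "at least 20 have to be non-smokers to detect a similar difference in exposure of 25" per cent. It does not restate a level. The total is capped: "In total we will include a maximum of 80 patients".

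Section 10 (Statistical analysis) plans a t test for each of two contrasts, namely clearance "in patients with a BMI < 20 compared to a BMI > 25 and for smokers versus non-smokers". It gives no significance level and no rule for the two tests taken together. Section 2 (Objectives) ranks BMI as primary and smoking as secondary.

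**The concern.** Two tests at two-sided 0.025 add up to 0.05, so the design looks like a Bonferroni split. If that is the intention, the fixed split leaves power unused. Once one hypothesis has been rejected at 0.025, the other can be tested at 0.05 without breaking the 5% family-wise limit.

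This matters more here than in many studies. The cohort is capped at 80 for financial reasons, so power cannot be bought with patients. The introduction also argues for an effect of BMI and an effect of smoking, and two real effects are the setting in which a stepwise rule gains.

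**Working it through.** **Inputs (section 4.4).** SD 25% of the mean, difference 25%, so standardised difference d = 25/25 = 1; power 0.8; two-sided level 0.025. Planned layout: 20 patients with BMI < 20 (about 5 smokers), 20 with BMI > 25 (about 5 smokers) and about 40 between (about 10 smokers), which gives 20 smokers and 60 non-smokers.

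**Step 1: reproduce the plan's figure.** n per group = 2(z₁₋α/₂ + z₀.₈)²/d².
- Level 0.025: 2(2.241 + 0.842)² = 19.01, so 20. The exact t test gives 20.3, and its power at 20 per group is 0.793.
- Level 0.05: 2(1.960 + 0.842)² = 15.7, so 16. The exact t test gives 16.7.

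The stated 20 fits 0.025 and not 0.05. So 0.025 is a genuine two-sided per-test level and not 5% written as a tail area.

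**Step 2: family-wise error.** Two tests at 0.025 have a family-wise error of at most 0.025 + 0.025 = 0.05, and 1 − 0.975² = 0.0494 if independent. Holm has the same bound under any dependence, which is needed because the two comparisons share patients. With no true effect, the chance of any false positive is identical under the two rules, since Holm's first step is the 0.025 test. Simulation of the planned layout (100,000 cohorts, normal data) gave 0.0493 for both.

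**Step 3: what Holm adds.** It rejects whatever the fixed rule rejects. It also rejects a hypothesis with p between 0.025 and 0.05 when the other p is below 0.025. Treating the tests as independent, power for BMI is

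P(p_BMI < 0.025) + [P(p_BMI < 0.05) − P(p_BMI < 0.025)] × P(p_smoking < 0.025).

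At d = 1, the BMI test (20 v 20) has power 0.7926 at 0.025 and 0.8690 at 0.05. The smoking test (20 v 60) has 0.9416 and 0.9689.
- BMI: 0.7926 + (0.8690 − 0.7926) × 0.9416 = 0.864.
- Smoking: 0.9416 + (0.9689 − 0.9416) × 0.7926 = 0.963.
- BMI when smoking has no effect: 0.7926 + 0.0764 × 0.025 = 0.7945.

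**Step 4: dependence on what the 25% includes.** Section 4.4 does not say whether its 25% variability already contains a smoking effect. If a 1-SD smoking effect comes on top, with 25% smokers in each BMI group, the added variance is 0.25 × 0.75 × 1² = 0.1875. The SD becomes √1.1875 = 1.09 and d falls to 1/1.09 = 0.92. If the 25% is the total, the residual variance is 1 − 0.1875 = 0.8125. Simulation of the 80-patient layout, with the middle BMI group set halfway between the extremes, covers both cases.

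| Both effects at 25% | BMI, fixed 0.025 | BMI, Holm | Smoking, fixed | Smoking, Holm |
|---|---|---|---|---|
| 25% total, independence formula | 0.79 | 0.86 | 0.94 | 0.96 |
| 25% total, simulated layout | 0.81 | 0.89 | – | gain about 2 points |
| Smoking effect adds variance, simulated | 0.73 | 0.82 | 0.92 | 0.95 |

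**Step 5: only one effect real (simulated).** With a BMI effect only, BMI power is about 0.79 under both rules (gain 0.1–0.2 points). The error on the null comparison rises from about 1.4–1.7% to 3.0–3.3%, below 5%.

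**The case against.** The strongest case against is that nothing here is wrong. A fixed 0.025 per test controls error, and the 20 per group follows from it. A more powerful valid rule does not turn a valid rule into a mistake. That stands, and so the point is an improvement only.

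A reader might infer more: that section 10 contradicts section 4.4, or that the analysis will run at 0.05 per test with a family-wise error near 1 − 0.95² = 9.75%. The protocol does not support this. Section 10 names no level other than the one in section 4.4, and restating a level may be left to a statistical analysis plan that is not at hand. The 9.75% describes a plan that nobody has written.

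Three further objections have weight.
- **The 5% family-wise aim is inferred.** The Summary calls the study explorative, and P < 0.025 stands only in the BMI paragraph. If 0.025 was meant as a stricter level for each comparison in its own right, Holm at 0.05 would loosen it.
- **Holm is not free of every cost.** It has no equally simple simultaneous confidence intervals, and its extra rejections include more false ones on a null comparison when the other effect is real. It also lets the threshold for the primary BMI test depend on the secondary smoking result.
- **Other valid rules exist.** Testing BMI first at 0.05 and then smoking at 0.05 would use the ranking in section 2. BMI power is then 0.869 at 20 per group, but smoking can be tested only if BMI is significant. Holm involves no such trade in power against the present rule.

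**Conclusion.** The point holds as an optional efficiency gain and not as an error in the protocol. Given an intended family-wise error of 5%, Holm never rejects less than the fixed 0.025 rule. The gain is about 7–9 points of power for BMI and about 2–3 points for smoking, provided that both effects reach the planned 25%. It is negligible if only one exists, and the chance of at least one rejection does not change in any scenario.

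These sizes rest on normal data, a standardised difference of 1, the planned 20/20/40 layout with 20 smokers and 60 non-smokers, and the reading of 0.025 as half of 5%. That last reading is well supported by the arithmetic but is stated nowhere in the protocol.

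**What to change.** State in section 10 that the BMI and smoking comparisons are tested two-sided with Holm's procedure at a family-wise level of 0.05: the smaller p-value is compared with 0.025 and, if it is significant, the other with 0.05. This also puts the 5% aim in writing.

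The calculation at 0.025 in section 4.4 stays as the worst case. The cost is one sentence, with no extra patients or data. If simultaneous confidence intervals matter more to the sponsor than the added power, keeping 0.025 for each test is a sound alternative, and section 10 should then say so.

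### The BMI comparison is sized on exposure but tested on clearance, with the scale and reference group of the 25% left open, so power at 20 per group is about 80% only under one unstated reading

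*Protocol*

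**What the plan says.** All references are to the protocol.

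- **Sample size calculation:** a "suggested inter-patient variability in fentanyl pharmacokinetics of 25" per cent, power 0.8 and "two-side testing (P <0.025" lead to at least 20 evaluable patients per group "to determine a difference in exposure between the two BMI-groups of 25" per cent. The same paragraph gives the purpose of Student's t test as "To evaluate the differences in plasma fentanyl concentrations".
- **Objectives:** the primary objective is met "by comparing the AUC between patients with a BMI < 20" and those with a BMI above 25.
- **Statistical analysis:** clearance is calculated for every sample, and Student's t test is then used "to compare the clearance for fentanyl in patients with a BMI < 20 compared to a BMI > 25". No transformation is mentioned. The section adds: "For all 4 of these groups at least 20 patients have to be included".
- **Introduction and rationale:** "We hypothesize that higher fentanyl concentrations will be reached when the patch is used by patients with thicker subcutaneous fat layers", with higher BMI standing for the thicker layer. No size is attached to this expectation.

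The primary comparison thus has three named variables: AUC, plasma concentration and clearance. Nowhere is it stated which BMI group the 25% is relative to, or whether the 25% variability is a fixed SD, a coefficient of variation (CV) or a log-scale SD.

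**The concern.** Each patient gives one sample under stable dosing. I therefore take apparent clearance to be the patch delivery rate divided by the concentration, which is the reciprocal of dose-normalised exposure. A percentage change in one is not the same percentage change in the other: exposure 25% higher is clearance 20% lower (1/1.25 = 0.80), and exposure 25% lower is clearance 33% higher (1/0.75 = 1.33).

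Two things are at stake. First, the stated 80% cannot be attached to the planned test without knowing the variable, the scale and the reference group. Second, an untransformed t test on a variable and one on its reciprocal are different tests of the same data. With both AUC and clearance named for the primary comparison, the significance verdict can depend on which is reported.

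**Working it through.** **Inputs.** From the sample size section: two-sided alpha 0.025, power 0.80, difference 25%, variability 25%, n = 20 per group. The direction for BMI (higher exposure at higher BMI) comes from the introduction. The scale of the variability and the reference group are not given, so each reading is computed.

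**1. The protocol's own figure.** Take the difference as 0.25 and the SD as 0.25 of the reference mean in both groups, so d = 0.25/0.25 = 1.

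- Normal approximation: n = 2(2.241 + 0.842)²/d² = 2 × 9.505 = 19.01, rounded up to 20 per group.
- Exact t test (noncentral t, 38 df, noncentrality d√(n/2) = √10 = 3.162): power at n = 20 is 79.3%, and 21 per group are needed for 80%.

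The figure of 20 reproduces. At two-sided 0.05 the normal formula would give 16, so 0.025 is the level that was used.

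**2. Exposure 25% higher than the reference (clearance 20% lower).** Standardised differences:

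- Exposure, CV 25% in each group: SDs 0.25 and 0.3125, pooled √((0.25² + 0.3125²)/2) = 0.283, d = 0.25/0.283 = 0.883.
- Clearance, CV 25% in each group: SDs 0.25 and 0.20, pooled √((0.25² + 0.20²)/2) = 0.226, d = 0.20/0.226 = 0.883.
- Log scale: SD = √ln(1 + 0.25²) = 0.246, d = ln(1.25)/0.246 = 0.906.
- Clearance, SD fixed at 25% of the reference mean: d = 0.20/0.25 = 0.80.

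| Reading | d | Exact t power, n = 20 | n per group for 80% |
|---|---|---|---|
| Exposure, SD fixed (protocol's figure) | 1.000 | 79% | 21 |
| Exposure, CV 25% in each group | 0.883 | 68% | 26 |
| Clearance, CV 25% in each group | 0.883 | 68% | 26 |
| Log scale | 0.906 | 70% | 25 |
| Clearance, SD fixed | 0.800 | 58% | 31 |

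Simulation with lognormal data (CV 25%, ratio 1.25, 200,000 trials) gives 68.6% for untransformed exposure, 68.6% for untransformed clearance and 70.1% on the log scale.

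**3. Exposure 25% lower than the reference (clearance 33% higher).**

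| Reading | d | Exact t power, n = 20 |
|---|---|---|
| Exposure or clearance, CV 25% in each group | 1.131 | 89% |
| Log scale: −ln(0.75)/0.246 | 1.168 | 91% |
| Clearance, SD fixed: 0.333/0.25 | 1.333 | 97% |

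**4. Ratio detectable with 80% power on the log scale.** At n = 20 and two-sided 0.025, 80% power needs d = 1.009. Then exp(1.009 × 0.246) = 1.28, and its reciprocal is 0.78.

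**5. Agreement of the two untransformed tests.** In lognormal simulations with CV 25%, ratio 1.25 and n = 20, the t tests on exposure and on clearance have equal power but reach different significance verdicts in about 8–9% of trials. At CV 40% the figure is about 12%. On the log scale the two variables differ only in sign and a constant once dose is divided out, so their p-values are identical.

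**The case against.** **There is no arithmetic error.** This stands. Twenty per group follows from the stated inputs, and the exact power of 79% is close enough to 80%. A reader might infer that the calculation is wrong; it is not.

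**The switch to clearance does not cause the loss of power.** This also stands in the main case. A reader might infer that power falls to 58–70% because the reciprocal is tested. With a 25% CV in each group, exposure and clearance have the same power, about 68–69%. The loss from 79% comes from letting the SD scale with the mean, and would arise equally if AUC were tested. The change of variable itself costs power (79% to 58%) only if the SD is held at 25% of the reference mean on both scales, which the protocol does not say.

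**The direction is not fixed.** The sample size section gives a two-sided difference with no reference group. The hypothesis in the introduction can equally be expressed as low-BMI exposure being 25% below high-BMI exposure. That is a ratio of 0.75, with 89–97% power. For smoking, the introduction points to lower exposure in smokers, which is again the favourable reading. So the documents do not support a flat statement that the study is underpowered.

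**A log transformation is commonly left to an SAP, and the study is exploratory with minimum group sizes.** This is fair, and the lack of the word log is not the point made here. What an unseen SAP does not remove is that the protocol itself names three variables for one comparison and ties its power to a different one from the variable it tests.

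**Conclusion.** The point holds as an inconsistency with measurable consequences. The comparison is planned on exposure, described as AUC and as plasma concentration, and tested as clearance, with the scale and reference group of the 25% unstated. Depending on the reading, power at 20 per group runs from 58% to 97%. With a 25% CV in each group and exposure 25% higher at high BMI relative to BMI below 20, it is about 68–70%, against the stated 80%.

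These figures assume the protocol's 25% variability, exactly 20 evaluable patients per group, dose-normalised exposure (patients enter irrespective of dose) and apparent clearance as rate over concentration. The simulated figures also assume lognormal data. The disagreement rate shows no bias in either test; it matters because the protocol leaves room to choose between them.

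**What to change.** 1. Name one primary variable, dose-normalised exposure or apparent clearance, and use it in the objectives, the sample size section and the statistical analysis section alike.
2. Analyse it on the log scale with the same t test, and report the geometric mean ratio between BMI groups, with the reference group named, and its confidence interval. The p-value is then the same for either variable, and power at a ratio of 1.25 is slightly higher (70% against 69% untransformed).
3. Restate the sample size section along these lines: at CV 25% and two-sided 0.025, 20 evaluable patients per group give about 80% power for a ratio of about 1.28 (or 0.78), about 70% for 1.25 and about 91% for 0.75.

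The cost is wording in these sections and a slightly less favourable power statement for a ratio of 1.25. No extra patients are needed if the restated detectable ratio is accepted. Keeping 80% power for a ratio of 1.25 on the log scale would instead take 25 per group.
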